### Data management

Data will be collected using electronic case record forms (e-CRFs) on the RedCap platform using either tablet computers or smartphones, leveraging the existing GARBH-Ini data management system. The database has a two-factor authentication and does not allow the storage of data on the local device. The schematic of the data management plan is outlined below, and a detailed data management plan has been formulated (
Figure 2).

**Figure 2. f2:**
[figure not shown]
Flow of data from clinical sites to centralized Data Management Centre at THSTI.

### Quality management protocol

A well-structured and detailed quality management plan has been developed, which includes of periodic monitoring activities at regular 15-day intervals both at the clinical sites as well as the home/workplace area. This is done to ensure that the quality and integrity of the data collected are in accordance with the study protocol, Standard Operating Procedures, Good Clinical Practice (GCP) guidelines, and applicable regulatory requirements. It is also intended to ensure consistency in the monitoring across all three sites. Additionally, 20% of the participants would also be contacted in a random order to inquire about the conduct of the study staff during the home visit process.

All study team members will be made familiar with and adhere to the National Ethical Guidelines for Biomedical and Health Research involving Human Participants, as well as the relevant protocol, applicable Standard Operating Procedures (SOPS), and Good Clinical Practice guidelines. The monitoring plan describes the tools to ensure the quality of the study, including that the rights, safety and well-being of the participants enrolled in the study are protected.

### Sample size

This exploratory study will be powered primarily on multiple physiological and biochemical outcomes, rather than on clinical endpoints, many of which currently lack sufficient preliminary data to enable formal power calculations at the 5% significance level.

Primary outcomes:

Physiological and biochemical measures include maternal core body temperature, urine specific gravity, maternal cardiac output (USCOM), heart rate variability, and angiogenic ratio (sFlt-1/PlGF). Clinical outcomes include preterm birth (<37 weeks of gestation) and birth weight (grams).

Secondary outcomes:

Secondary endpoints comprise gestational age (weeks), small for gestational age (SGA), stillbirth, and additional placental and fetal biomarkers.

A total of 700 pregnant women will be enrolled to account for an anticipated attrition rate of approximately 15%, yielding an expected final sample of about 600 mother–baby dyads with complete follow-up. The majority of outcomes are continuous variables, which—following transformation to approximate normality, if required—will provide 80% statistical power at a two-sided significance level of α = 0.05 to detect a minimum difference of 0.23 standard deviations between high versus low heat exposure groups. This detectable effect size lies well within accepted thresholds for clinical relevance.

### Statistical approach

The study team will implement a pre-specified Statistical Analysis Plan (SAP), finalized and published prior to database lock, to quantify associations between environmental exposures—heat, humidity, and ambient PM
_2.5_—and maternal, fetal, placental, and early lactational physiological outcomes. Analyses will follow a hierarchical framework (primary, secondary, exploratory) with clearly defined endpoints to manage multiplicity. Data will undergo standardized procedures for cleaning, validation, and coding. Patterns of missingness will be described, and multiple imputation will be applied where appropriate. All model assumptions (normality, collinearity, linearity) will be evaluated systematically.

Primary Analytical Framework – Mixed-Effects Models:

Given the longitudinal and multi-site design of the HiP-India study, mixed-effects models (LME, GLMM, GAMM) will constitute the core analytic approach.

Random effects: Site-level random intercepts will account for geographic and climatic clustering across Gurugram, Puducherry, and Chhattisgarh, while subject-level random intercepts and slopes will capture individual differences in heat-response trajectories.

Serial correlation: Autoregressive structures (e.g., AR(1)) will model correlations between repeated trimester-specific measurements.

Time-varying exposures: Trimester-specific heat exposure estimates will be modeled as time-varying covariates to assess both immediate and cumulative effects.

Model flexibility: Linear mixed models will be used for continuous outcomes (e.g., physiological measures, biomarkers), generalized linear mixed models for binary outcomes (e.g., preterm birth, SGA), and generalized additive mixed models where non-linear exposure–response patterns are expected.

Complementary Distributed Lag Non-Linear Models (DLNM):

DLNM will be employed to examine delayed and non-linear exposure–response relationships across gestation.

Lag structure: Lags will extend from enrolment through outcome ascertainment, capturing both short-term (≤28 days) and longer-term (up to ~20 weeks) effects.

Basis functions: Natural cubic splines with empirically derived knots will model non-linear exposure and lag responses.

Temporal alignment: Exposure windows will be aligned primarily by calendar date to preserve seasonal context, and secondarily by gestational age to identify sensitive developmental periods. Hybrid alignment approaches will also be considered.

Direct Acylic Graph (DAG)-Guided Confounder Control and Effect Modification Strategy:

A tentative DAG has been developed to inform model specification and covariate adjustment (
Figure 3). The minimal sufficient adjustment set includes:

Site (geographic clustering), maternal age, education level, occupation type, family income/socioeconomic status, nutritional status, housing quality (ventilation, overcrowding), season/recruitment timing, parity, and indoor air pollution exposure (biomass fuel use, passive smoke).

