### Study setting

The three study locations were selected to represent distinct climate zones across India, each with unique environmental exposures relevant to maternal and child health. Gurugram is located within the Delhi National Capital Region (NCR) and experiences a
**semi-arid climate**, characterised by extreme temperature variations, with scorching summers, cold winters, and limited rainfall, resulting in prolonged dry spells and frequent heatwaves. Chhattisgarh represents a
**humid subtropical to tropical wet and dry climate**, marked by high humidity, hot summers, and a well-defined monsoon season, creating conditions of alternating intense heat and moisture. Puducherry, situated along the southeastern coast, exemplifies a
**tropical wet and dry climate**, with persistently high temperatures, elevated humidity, and pronounced monsoon periods, particularly during the northeast monsoon. These diverse climatic conditions provide a natural contrast in thermal environments, enabling the study to capture a range of heat exposures and their differential impacts on pregnancy-related outcomes across varying ecological contexts.

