**ASSESSMENTS**						
Clinical history		X	X	X	X	
Food frequency questionnaire		X	X	X		
Heat exposure and indoor pollution measurements		X	X	X		X
Modified HOTHAPS questionnaire		X	X	X		
Urine specific gravity		X	X	X		
Maternal Haemodynamic assessment		X	X	X		
Fetal Ultrasound		X	X	X		
CTG				X		
Maternal blood sample		X	X	X		
Birth and newborn outcomes					X	
Lactation study (100 women only in GCH)					X	X

**Table 2. T2:** List of planned clinical samples with their processing methods and planned future course of analysis.

The sample collection, processing methods are summarized in Table 4: Biospecimen	Time of collection	Method of collection	Immediate processing at study site	Transportation time to storage at biorepository	Long term storage	Studies*
Maternal Blood -5 ml (EDTA tube)	11–14 weeks 18–22 weeks 30–34 weeks Time of Delivery	Venepuncture	1. Stored as buffy coat 2. Processed to plasma	In liquid nitrogen (-196 ° C) / within 8 hours for GCH site and in Dry Ice for other two sites	Deep freezers (-75 °C)	Biobanking, biochemistry,
Maternal Blood (plain tube) – 5 ml	11–14 weeks 18–22 weeks 30–34 weeks Time of Delivery 15 days post delivery (pre and post feed)	Venepuncture	Processed to sera	In liquid nitrogen (-196 ° C) / within 8 hours for GCH site and in Dry Ice for other. two study sites	Deep freezers (-75 °C)	Biobanking, biochemistry,
Breast milk	First and 15 days post delivery	Manual expression	Stored in 0.5 ml aliquots up to a total volume of 5 ml	In liquid nitrogen (-196 ° C) / within 8 hours for GCH site and in Dry Ice for other. two study sites	Deep freezers (-75 °C)	Biobanking, biochemistry

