**Figure 3. f3:**
[figure not shown]
Tentative DAG to handle confounders in the analysis.

PM
_2.5_ Treatment Strategy:

Primary analysis: PM
_2.5_ will be modeled as an effect modifier (Heat × PM
_2.5_ interaction).

Secondary analysis: If significant interaction is not detected, PM
_2.5_ will be adjusted as a confounder in sensitivity models.

Justification: Both exposures may exert synergistic biological influences on maternal thermoregulation and hemodynamics.

Prespecified Interactions and Stratifications:

Interactions to be formally tested include:

Heat × PM
_2.5_ (synergistic effects on maternal hemodynamics), Heat × Site (climate adaptation differences), Heat × Season (acclimatization effects), Heat × Occupation (differential vulnerability by work environment), and Heat × Housing Quality (thermal protection efficacy).

Stratified analyses will be conducted by site (Gurugram, Puducherry, Chhattisgarh), recruitment season (warm vs. cool), occupation (high-risk vs. lower-risk), housing quality (traditional vs. modern materials), and gestational timing (early vs. mid vs. late pregnancy enrolment).

Mediation and Sensitivity Analysis Framework:

The study design facilitates mediation analysis through temporally aligned data collection, with personalized exposure monitoring, blood pressure measurement, biomarker sampling, and clinical assessment conducted synchronously at three points across pregnancy. This alignment strengthens the exposure → mediator → outcome temporal sequence and reduces bias from measurement misalignment.

To address unmeasured confounding, the analysis will consider negative control approaches using biomarkers or outcomes theoretically unrelated to the heat–hemodynamic pathway, supplemented by mediational E-values to quantify the magnitude of unmeasured confounding required to alter results. The multi-site structure enables leveraging geographic and seasonal variation as natural experiments to test mediation assumptions.

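### Site, a confounder tied to heat by design, is adjusted for through a random intercept with only three levels; it should be a fixed factor

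*Protocol article*

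**What the plan says.** The site term is specified in the mixed-model part of Statistical approach: "Site-level random intercepts will account for geographic and climatic clustering across Gurugram, Puducherry, and Chhattisgarh". At the level of the woman, "subject-level random intercepts and slopes will capture individual differences in heat-response trajectories", and for the repeated measures, "Autoregressive structures (e.g., AR(1)) will model correlations between repeated trimester-specific measurements".

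Site appears in two further places. The DAG-guided adjustment set opens with "Site (geographic clustering), maternal age, education level, occupation type" and does not say whether site is coded as fixed or random. The list of prespecified interactions includes "Heat × Site (climate adaptation differences", and analyses stratified by site are planned as well.

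Study setting explains how the sites were chosen: "The three study locations were selected to represent distinct climate zones across India". Table 2 gives the sampling times as "11–14 weeks 18–22 weeks 30–34 weeks Time of Delivery".

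**The concern.** A random intercept is a sound way to handle many sites drawn from a population, with effects unrelated to the exposure. Neither condition holds here. There are three sites, chosen on purpose, and the reason for choosing them (climate) is the exposure under study.

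The sites differ in other ways that could move the outcomes. They differ in level of care and recruitment route (Study setting). They also differ in sample transport: Table 2 gives liquid nitrogen within 8 hours for the Gurugram site and dry ice for the other two. Transport could affect biomarkers such as the sFlt-1/PlGF ratio, which is a primary outcome.

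A random intercept removes between-site differences only to the extent that the estimated site variance is large. If the estimate is zero, site is not adjusted for at all. If it is small, part of the between-site contrast, with everything else that differs between the sites, is counted as an effect of heat. At stake is the pooled heat estimate and the error rate of its test.

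**Working it through.** **1. The article's own figure.** Sample size states 0.23 SD, 80% power, two-sided 0.05 and about 600 completers; the Structured summary gives 300 per season group. The number per group is 2 × (1.960 + 0.842)² / 0.23² = 297. With 300 per group, power is 80.4% and the detectable difference is 0.229 SD. The figure reproduces.

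**2. Precision of the site variance.** Three sites give 2 degrees of freedom. Even ignoring within-site noise, the 95% interval for the site SD runs from √(2/7.378) = 0.52 to √(2/0.0506) = 6.3 times the estimate.

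**3. Chance of a zero estimate.** Assumptions, not in the documents: 200 women per site (600/3), one outcome per woman, and site SD τ in units of the within-site outcome SD. In a balanced one-way layout the estimate is zero when the between-site mean square falls below the within-site one, so P(zero) = P(F(2, 597) < 1/(1 + 200τ²)).

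| τ | 1/(1 + 200τ²) | P(zero) |
|---|---|---|
| 0.05 | 0.667 | 49% |
| 0.10 | 0.333 | 28% |
| 0.20 | 0.111 | 10% |

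**4. Effect on the heat test.** Simulation with true heat effect zero and 200 women at each of three sites. Site heat means are −1.22, 0 and +1.22 within-site SD, and site effects run in the same direction (−1.22τ, 0, +1.22τ). The random-intercept model is fitted by REML and compared with fixed site. Each cell gives 400 runs / a repeat with 4,000 runs per setting.

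| Site SD | Mean heat estimate, random site | Type I error, random site | Type I error, fixed site |
|---|---|---|---|
| 0.10 | 0.023 / 0.024 | 19% / 19% | 4.5% / 4.5% |
| 0.15 | 0.021 / 0.024 | 17% / 19% | 4.8% / 4.4% |
| 0.20 | 0.018 / 0.018 | 12% / 14% | 4.3% / 4.7% |
| 0.30 | 0.010 / 0.012 | 7% / 8% | 3.7% / 5.1% |
| 0.50 | 0.009 / 0.008 | 5% / 6% | 2.8% / 5.3% |

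Monte Carlo error with 400 runs is about ±2 points at 5% and ±4 points at 19%. With fixed site the mean heat estimate was zero to within simulation error.

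The mean bias is small because it averages runs with near-full adjustment and runs with little or none. With no site term, the expected slope at site SD 0.10 is between-site covariance over total heat variance: 0.10/(1 + 1) = 0.05, with a standard error of 1/√(600 × 2) = 0.029.

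The result depends on how far apart the sites are in heat. Halving the separation to ±0.6 lowers type I error under the random intercept to about 8% at site SD 0.10 and 0.15, and 6% at 0.20 and 0.30 (4,000 runs). With the original separation but site effects drawn at random, it was about 7% to 10% at site SD 0.10 to 0.30 across the two sets of runs.

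**5. Visit spacing (minor).** Window midpoints are 12.5, 20 and 32 weeks, so the gaps are 7.5 and 12 weeks, a ratio of 1.6. If residual correlation decays with elapsed time and is 0.5 over the first gap, it is 0.5^1.6 = 0.33 over the second. AR(1) by visit order uses 0.5 for both.

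**The case against.** The strongest reply is that the harm is limited where it is likeliest. A zero variance estimate is commonest when the sites hardly differ, and then omitting site matters least. The bias found is about 0.02 SD per within-site SD of heat. The inflated test error rests on assumed site sizes, site effects and heat separation, and shrinks when the separation is halved. Warm and cool recruitment at every site (Inclusion criteria) gives within-site contrast, and the stratified analyses hold site constant. All of this stands and limits the size of the point. It does not rescue the pooled core estimate, because the stratified analyses are separate from it.

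A second reply is that fixed site discards between-site heat contrast, which the design values. That is a real trade-off. But this contrast rests on three sites and cannot be separated from whatever else differs between them.

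Some stronger readings are tempting but not supported:

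- *Site is used twice, as random and as fixed.* The adjustment set never says fixed, and the random intercept may be how that entry is meant to be met. Redundancy and loss of adjustment also exclude each other: if site were fixed as well, its adjustment could not drop out.
- *The model is over-specified.* With a slope on time, random intercept and slope (3 parameters), residual variance (1) and AR(1) (1) make five, against six distinct variances and covariances from three visits. That is identified, though weakly. A slope on heat would be better identified.
- *AR(1) forces equal correlation between visits.* It is given only as an example, and on top of random effects it constrains the residual correlation, not the total.
- *Woman-level effects are applied to birth weight or preterm birth.* No text says so; serial correlation is tied to repeated measurements.

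**Conclusion.** The point holds for the site term. The article commits its core models to a random intercept over three named sites, selected for climate, while treating site as a confounder of heat. This is a stated choice, not a detail left to the SAP.

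If site is random only, there is a material chance that its adjustment disappears (28% at a site SD of 0.1). In the aligned simulation, type I error is two to four times nominal at site SDs of 0.10 to 0.20, falling towards nominal at larger ones. Bias is small throughout. These sizes rest on 200 women per site, one outcome per woman, a site heat separation of about ±1.2 within-site SD, and site effects that run with site heat. None of these is given in the document. The case for changing the term does not depend on the exact values, because three purposively chosen levels cannot support a variance component used for confounder control.

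The visit-spacing remark is minor.

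**What to change.** Enter site as a fixed factor (two indicators) in every pooled model, drop the site random intercept, and build the planned Heat × Site test on those terms. State this once, so that the random-effects paragraph, the adjustment set and the interaction list agree.

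For outcomes repeated across the three visits, prefer an unstructured within-woman covariance, or a continuous-time autoregressive one in gestational weeks, to AR(1) by visit order.

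Cost: a change of wording, made in the SAP before database lock. It uses two of about 600 degrees of freedom, so the detectable difference stays at about 0.23 SD before any loss from correlation between heat and site. That loss can matter for measured heat. Under the separation assumed above, the standard error per within-site SD of heat is 1/√600 = 0.041 with fixed site, against 0.029 with no site term. Inference is then explicitly for these three sites, and the main estimate uses within-site heat contrast only. If the between-site contrast is of interest, report it separately and label it as confounded with site.

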### Fetal and placental ultrasound and CTG assessments

It is also hypothesised that ambient heat exposure could alter Uterine Artery (UtA) flow, which in the first trimester could lead to poor trophoblast invasion, and increased risk of preeclampsia and other placental disorders
^
12
^, whilst later in pregnancy could alter umbilical artery Doppler readings. This reduction in perfusion could lead to lower fetal oxygen levels, causing blood redistribution to vital organs, which is detectable as changes in the middle cerebral artery (MCA) Doppler and the cerebroplacental ratio (CPR). The latter is a key predictor of perinatal morbidity and mortality in fetuses at risk for growth restriction
^
13,
14
^. Chronic exposure to heat with fetal blood flow redistribution could lead to reduced fetal growth
^
15,
16
^.

The detailed imaging protocol is reported elsewhere
^
7
^, but in brief the study will use trasnadominal two-dimensional ultrasound to obtain the key ultrasound parameters of the following:

At 11–14 weeks of gestation

- Crown-rump length (CRL) for pregnancy dating
^
17
^- conducted between 9 to <14 weeks and is used for all subsequent analyses, including preterm birth classification.

At each subsequent ultrasound assessment

- Biparietal diameter (BPD), head circumference (HC), abdominal circumference (AC) and femur length (FL) for biometry- Estimated fetal weight (EFW)- Amniotic fluid index easurement (AFI)- Maternal cervical length- Blood flow assessment using color flow Doppler of the Uterine artery at 18–22 and 30–34 weeks of gestation- Umbilical artery at 30–34 weeks of gestation- MCA and calculation of CPR at 30–34 weeks of gestation

In addition to the routine, detailed fetal anatomical survey performed at the second-trimester scan according to standard protocol, we will confirm that a basic structural assessment is conducted to identify any major congenital anomalies. At the same examination, placental characteristics—including location, morphology and biometric measurements—will be recorded to ensure we capture any exposure‐related vascular or placental changes.

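### SGA, the only named birth outcome scaled to gestational age, is analysed as yes/no; adding the z-score behind it would cheaply recover power

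*Protocol article*

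**What the plan says.** All references are to the Protocol article.

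- **Sample size, primary outcomes.** After the physiological and biochemical measures: "Clinical outcomes include preterm birth (<37 weeks of gestation) and birth weight (grams").
- **Sample size, secondary outcomes.** "Secondary endpoints comprise gestational age (weeks), small for gestational age (SGA), stillbirth, and additional placental and fetal biomarkers".
- **Statistical approach, model flexibility.** Linear mixed models are planned for continuous outcomes, and "generalized linear mixed models for binary outcomes (e.g., preterm birth, SGA").
- **Fetal and placental ultrasound and CTG assessments.** The growth hypothesis is stated here: "Chronic exposure to heat with fetal blood flow redistribution could lead to reduced fetal growth". The same section lists biparietal diameter, head and abdominal circumference, femur length and estimated fetal weight at the scans after 11–14 weeks. Table 1 places the last of these at 30–34 weeks.
- **Confounder control.** Gestational age at birth is not in the listed minimal adjustment set.

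The article does not name a birth-weight-for-gestational-age z-score or centile as an outcome.

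**The concern.** SGA is a cut on a continuous quantity, birth weight relative to gestational age. Reducing that quantity to yes/no discards information on how far each baby lies from the cut. That matters most when the expected effect is a modest shift of the whole distribution, which is how the sample-size statement describes effects.

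The other named birth outcomes do not replace it. Grams fall both when a fetus grows more slowly and when it is born earlier. Gestational age and preterm birth measure timing alone. The study sets out to identify pathways from heat to adverse outcomes, so growth and timing need to be told apart. The study's ultrasound measures do address growth on a continuous scale, but growth after the 30–34 week scan is seen only at birth.

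At stake is a null SGA result that carries little information at the effect size the study was designed around.

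**Working it through.** **Inputs from the document (Sample size, except the split)**
- Test: "two-sided significance level of α = 0.05".
- Power: "will provide 80% statistical power".
- Effect: "to detect a minimum difference of 0.23 standard deviations between high versus low heat exposure groups".
- Analysed number: "yielding an expected final sample of about 600 mother–baby dyads with complete follow-up".
- Split: the Structured summary gives 300 summer and 300 winter participants. I take the same even split for high against low exposure.

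**Inputs assumed**
- SGA prevalence in the low-exposure group is not given. I vary it from 5% to 50% and treat 10% to 45% as the working range.
- z-scores are normal, and exposure moves the whole distribution by 0.23 of its SD.
- Groups are compared without adjustment, as in the plan's own power statement.

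**Step 1: reproduce the plan's figure.** Power = Φ(d·√(n/2) − 1.96) with d = 0.23 and n = 300. Here 0.23 × √150 = 2.817, and Φ(2.817 − 1.960) = 0.804. The required number is 2 × ((1.960 + 0.842)/0.23)² = 297 per group. The stated 80% at 0.23 SD is reproduced. A z-score analysed as a continuous outcome would have this power.

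**Step 2: read the same shift through the SGA cut.** If low-exposure prevalence is p₁, high-exposure prevalence is p₂ = Φ(Φ⁻¹(p₁) + 0.23). With p̄ the mean of the two,

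power = Φ( [ |p₂ − p₁| − 1.96·√(2p̄(1−p̄)/n) ] / √( [p₁(1−p₁) + p₂(1−p₂)]/n ) ).

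| p₁ | p₂ | SGA power | Loss against 80.4% (points) |
|---|---|---|---|
| 5% | 7.9% | 29.6% | 50.8 |
| 10% | 14.7% | 41.0% | 39.4 |
| 15% | 21.0% | 48.1% | 32.3 |
| 20% | 27.0% | 52.9% | 27.5 |
| 30% | 38.4% | 58.5% | 21.9 |
| 40% | 49.1% | 60.9% | 19.6 |
| 45% | 54.2% | 61.2% | 19.3 |
| 50% | 59.1% | 61.0% | 19.5 |

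For 80% power, SGA would need 784 per group at 10%, 569 at 20%, 497 at 30% and 471 at 40%, against 297 for the z-score.

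**Step 3: vary the size of the shift.** With a uniform 0.30 SD shift, z-score power is 95.7%, and the loss over 10% to 45% prevalence is about 33 down to 12 points.

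**Step 4: concentrate the effect in a subgroup.** For illustration, put the same mean shift in 15% of exposed fetuses, so that each moves 0.23/0.15 = 1.53 SD. The exposed-group variance becomes 1 + 0.15 × 0.85 × 1.53² = 1.30, and power on the mean z-score is Φ(0.23/√((1 + 1.30)/300) − 1.96), about 75%. SGA prevalence in the exposed group is 0.85·p₁ + 0.15·Φ(Φ⁻¹(p₁) + 1.53). At p₁ = 10% this is 17.5% and SGA power is about 76%, so the loss disappears. At 20% the loss is about 8 points and at 30% about 19.

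**Step 5: what grams already recover.** Suppose the z-score shifts by 0.23 SD, gestation is unaffected, and birth weight correlates ρ with gestational age. The standardised effect on grams is 0.23·√(1 − ρ²). For assumed ρ of 0.3 it is 0.219 (power about 77%); for 0.7 it is 0.164 (about 52%).

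**The case against.** The strongest reply has four parts.

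**Growth is tested elsewhere on a continuous scale.** Biometry and estimated fetal weight are repeated, dated by crown-rump length, and suited to the planned linear mixed models. This stands. A reader might infer that the fetal-growth hypothesis rests on SGA alone; the article does not support that. What remains is growth after the last study scan.

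**Birth weight in grams is continuous and ranks above SGA.** This also stands, and Step 5 shows that it recovers part of the loss. A reader might go further and say that growth and early delivery could never be separated. That is too strong: gestational age is measured and is itself a secondary outcome, and mediation analysis is planned. The fair statement is that the article does not name an analysis making this separation for size at birth.

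**The study is exploratory and says it is not powered on clinical endpoints.** True. The 0.23 SD statement concerns continuous outcomes and promises nothing for SGA. It would be wrong to conclude that the power statement is in error.

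**The model list is illustrative and an analysis plan will follow.** The text gives SGA as an example in a condensed article, and the unseen plan may add a z-score. So the article cannot be said to rule one out. It does name the secondary endpoints and pairs SGA with a binary model, and that is the choice addressed here.

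SGA is also a clinical outcome of interest in its own right, listed as such in the Abstract and Background. Nothing here argues for dropping it or reducing it to description.

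**Conclusion.** The point holds as an improvement to the plan, not as the correction of an error. Among the named birth outcomes, only SGA is relative to gestational age, and it is assigned a binary analysis. At the plan's own 0.23 SD, that analysis would have about 41% to 61% power where the z-score would have about 80%, a gap of about 19 to 39 points.

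The range depends on an assumed SGA prevalence of 10% to 45%, a uniform normal shift, and an even unadjusted split. It is wider at lower prevalence and narrower for larger shifts; for an effect concentrated in a subgroup it can vanish. It compares two ways of analysing one quantity, so it should not be read as what the whole plan loses: grams and the ultrasound measures carry some of that information. The gain that does not depend on these figures is interpretive, a continuous measure of size at birth that is not driven by timing of delivery.

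**What to change.** In Sample size (secondary outcomes) and Statistical approach, add the birth-weight-for-gestational-age (and sex) z-score as a continuous secondary endpoint. Take it from the same standard used to define SGA, and analyse it with the linear model already planned for continuous outcomes. Keep SGA as a reported binary secondary outcome, and leave preterm birth and birth weight in grams as they are. State that the conclusion on growth at birth will rest mainly on the z-score, read together with the ultrasound growth measures.

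The cost is a few lines of wording and one derived variable; birth weight, dated gestation and a size standard are already needed to assign SGA. The downsides are one more secondary endpoint in the hierarchy and a result, a mean z-score difference, that is less directly clinical than a risk. Reporting SGA beside it meets the second. Because the article says the analysis plan will be finalised before database lock, the addition can still be made in advance.
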